### Sample size calculation

A total of 2600 new TB patients will be eligible and consent to be screened for alcohol misuse over a period of six months. Assuming that 20% screen positive for problem drinking, 520 new TB patients will enter the study. A minimum of 13 patients will be recruited from each of the 42 primary care clinics. It is expected that 10% of participants may be lost prior to completing the 3-months and 6-months follow-up assessments so that the final sample would be 468.

Based on the current AUDIT score of 12 among TB patients, it is assumed that the intervention will reduce the current AUDIT score by 12% to 10.6 [32,33]. Based on this assumption and taking account of the design effect of 2 to account for intraclass correlations expected from participants from the same area and followed up over time the estimated sample size of 452 will allow us with 80% power (5% level of significance) to detect the difference of 12% between the two groups.

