**Methods/Design:**

Within each of the three selected health districts with the highest TB burden in South Africa, 14 primary health care clinics with the highest TB caseloads will be selected. Those agreeing to participate will be stratified according to TB treatment caseload and the type of facility (clinic or community health centre). Within strata from 14 primary care facilities, 7 will be randomly selected into intervention and 7 to control study clinics (42 clinics, 21 intervention clinics and 21 control clinics). At the clinic level systematic sampling will be used to recruit newly diagnosed TB patients. Those consenting will be screened for alcohol misuse using the AUDIT. Patients who screen positive for alcohol misuse over a 6-month period will be given either a brief intervention based on the Information-Motivation-Behavioural Skills (IMB) Model or an alcohol use health education leaflet.

A total sample size of 520 is expected.

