### Procedure

Universal screening of all new tuberculosis treatment patients will be used whereby all consecutive clients visiting the primary health care facility will be screened for alcohol problems and be offered a brief counselling intervention. A health care provider who identifies a new TB treatment patient (within one month on treatment) will inform the patient about the study and refers the patient for participation if interested. A research assistant will ask for permission/consent from patients attending the primary care facility to participate in the stage 1 of the study, i.e. screening or baseline assessment using the AUDIT questionnaire. This will take about 15 minutes. The research assistant will not be involved in delivering the brief counselling intervention. All participants undergo the initial assessment and the research assistant will score the results of the alcohol test section of the questionnaire. Tuberculosis patients who will score 8 or more for men and 7 or more for women on the AUDIT questionnaire after screening (risky drinkers) will then be approached by the research assistant for a second informed consent for enrolment in stage 2, the intervention study. For patients included in the study, the research assistant refers the patient to a clinic counsellor who carries out the intervention (experimental or control) for all the participants after which they will be followed up at 3 months and 6 months at the health facility, and assessments will be done by the research assistant. The experimental intervention includes a brief counselling intervention on alcohol risk reduction consisting of two sessions, the first immediately after alcohol screening and the second within a month thereafter. In the control condition the clinic counsellor provides an alcohol education leaflet, and after completion of the 6 months follow-up, the trained clinic counsellor will provide the delayed intervention of brief counselling intervention on alcohol risk reduction. At follow-up at least six individual attempts are made to contact patients by telephone and letter. Even if a contact was not successful at 3 months, further attempts will be made at 6 months. Sampling will occur throughout all hours of clinic operation over a 6 months period. Thirteen tuberculosis patients will be recruited from each primary health care facility (n = 13). Participants will receive Rand 60 (8.5 US$) transport reimbursement at 6-month follow-up (see Figure 1).

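### The stated enrolment of 520 contradicts at least 13 patients in each of 42 clinics (546), and the recruitment chain makes no allowance for refusal of the second consent

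*Protocol article*

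**What the plan says.** The Sample size calculation section starts from screening: "A total of 2600 new TB patients will be eligible and consent to be screened for alcohol misuse over a period of six months". It continues: "Assuming that 20% screen positive for problem drinking, 520 new TB patients will enter the study". It then deducts 10% for loss to follow-up, reaching a final sample of 468, and sets this beside a required sample of 452 for 80% power at the 5% level with a design effect of 2.

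Between those steps it adds a clinic quota: "A minimum of 13 patients will be recruited from each of the 42 primary care clinics". The Procedure section gives the same number as a fixed count rather than a minimum: "Thirteen tuberculosis patients will be recruited from each primary health care facility (n = 13". The abstract has "42 clinics, 21 intervention clinics and 21 control clinics" and then "A total sample size of 520 is expected".

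On enrolment, the Procedure section says that patients at or above the AUDIT cut-off "will then be approached by the research assistant for a second informed consent for enrolment in stage 2, the intervention study". The Consent section confirms the two stages: one consent for the screen, and another after a positive AUDIT that covers contact details, the allocated condition and both follow-ups.

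**The concern.** Two things do not fit together.

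First, a floor of 13 in every one of 42 clinics cannot be reconciled with a total of 520. A site team following the quota and one following the total would stop recruiting at different points, and the planned screening volume supports only the total.

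Second, the consent counted in the sample size section is consent to be screened. The later consent, which decides who enters the trial, has no place in the chain, so the 520 amounts to an assumption that nobody declines. At stake are the enrolled and evaluable numbers that the trial reports as its plan, and the power attached to them.

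**Working it through.** **Inputs from the protocol article.** Screened 2600; screen-positive 20%; entering 520; loss 10%; final sample 468; required 452; power 80%; significance level 5% (two-sided assumed, since the article does not say); design effect 2; 42 clinics; 13 per clinic. No second-consent rate is given, so the rates below are assumptions shown as a range.

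**1. The plan's own chain.**
- 2600 x 0.20 = 520
- 520 x (1 - 0.10) = 468

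Both reproduce exactly. The margin over 452 is 468 - 452 = 16 evaluable patients.

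**2. The clinic quota.**
- 42 x 13 = 546, which is 26 patients (26/520 = 5.0%) above 520
- 520/42 = 12.4 per clinic; 520/13 = 40 clinics
- To enrol 546 with no refusals: 546/0.20 = 2730 screened, or 546/2600 = 21.0% of those screened
- 546 x 0.90 = 491 evaluable, above both 468 and 452

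**3. Room for refusal at the second consent.**
- If 452 is evaluable: 452/0.90 = 502.2, so 503 must enrol. 520 - 503 = 17 may refuse, and 17/520 = 3.3%.
- If 452 is enrolled: 520 - 452 = 68 may refuse, and 68/520 = 13.1%.

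**4. Power if some refuse.** Taking 452 as evaluable with 80% power at design effect 2, the effective sample is 452/2 = 226. The SD and the difference cancel when power is expressed relative to that point:

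power = Φ(2.802 x √(N_eff/226) - 1.960), where N_eff = evaluable N / design effect and 2.802 = 1.960 + 0.842.

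(a) Design effect held at 2:
- 90% consent: 520 x 0.90 x 0.90 = 421.2; N_eff = 210.6; power = Φ(0.745) = 77%
- 80% consent: 520 x 0.80 x 0.90 = 374.4; N_eff = 187.2; power = Φ(0.590) = 72%

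(b) Design effect falling with cluster size, read as 1 + (m - 1) x ICC. At 452/42 = 10.76 per clinic, a design effect of 2 implies ICC = 1/9.76 = 0.102.
- 90% consent: m = 421.2/42 = 10.03; design effect 1.92; N_eff about 219; power = Φ(0.80) = 79%
- 80% consent: m = 374.4/42 = 8.91; design effect 1.81; N_eff about 207; power = Φ(0.72) = 76%

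**The case against.** The strongest reply is that this is a rounding slip with no consequence. On that view 13 is 12.4 rounded up, the error is on the favourable side, and meeting it would leave 491 evaluable patients. The reply is right that the mismatch alone does not endanger power. It does not remove the contradiction: a minimum cannot be an average rounded up, and the planned screening does not supply 546.

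It can also be said that the word eligible in the sample size section already absorbs losses before enrolment. It may cover the other exclusions, such as pregnancy or current alcohol treatment. It cannot cover the second consent, which is sought only after the AUDIT has been scored.

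Several stronger readings are tempting, and the document does not support them:
- A reader might infer that the planned screening fails to deliver the stated sample. It does deliver 520 and 468; only the quota of 13 per clinic is out of reach.
- A reader might infer that the power claim rests on too small an SD, since 452 implies about 3.8 points. The article states no SD and cites sources for its assumption. A condensed article may leave that detail out, and nothing in it shows 3.8 to be wrong.
- A reader might infer that controls are assumed not to change, because the fall from 12 to 10.6 in the intervention arm becomes the contrast. But the section states its target as "to detect the difference of 12% between the two groups", which is already a between-arm quantity. Any smaller difference would be the reader's own figure.
- A reader might calculate the share of clinics that would miss 13. That needs equal clinic sizes and one common positive rate, whereas the clinics are stratified by caseload.

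**Conclusion.** The point stands as an internal contradiction plus an omitted step. The enrolment figures disagree by 26 patients (5%), and the stated screening cannot meet the stated minimum per clinic. The chain also treats all 520 screen-positive patients as entrants despite the protocol's own second consent.

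How tight this is depends on what 452 counts. Evaluable is the natural reading, because 452 follows the final sample after loss, but the article does not say so. The tolerance for refusal is 3.3% on that reading and about 13% if 452 means enrolled. Both figures take 2600, 20% and 10% at their planned values.

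The cost in power is a gentle slope: relative to 80%, about 1 to 3 percentage points at 90% second consent and about 4 to 8 at 80%. The lower loss applies if the design effect shrinks with cluster size. The article attributes the design effect partly to repeated follow-up, so neither version can be preferred from the text. This calls for a correction to the sample size statement; it does not show that the trial is seriously underpowered.

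**What to change.** Keep 2600 screened and 20% positive, and give one chain: screened, screen-positive, second-consent rate, enrolled, loss, evaluable. In both the Sample size calculation and Procedure sections, replace the 13 per clinic with an average that follows from the chain: about 12 before refusals (520/42 = 12.4), and for example 468/42 = 11.1 at 90% second consent. State whether 452 is evaluable or enrolled. Then restate enrolled N, evaluable N and the resulting power, saying whether the design effect of 2 is held fixed, and bring the abstract's total into line.

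This costs rewording and a short recalculation. It needs no extra patients, and the stated power becomes slightly less favourable. Keeping 13 per clinic instead would not be free: it needs at least 2730 screened, and more once refusals are counted (for example 2730/0.90 = 3033 at 90% second consent).

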### Data analyses

Cluster-specific methods of data analysis will be used because we will randomize clinics rather than patients.

#### Intention to treat

The principle of the statistical analysis will be intention to treat. It will be applied to the two hierarchical levels of the trial: the clinics randomized at the cluster level and the patients recruited within each of these units.

##### Clinic level

All units randomized will be included in the analysis. Units will be analyzed according to the intervention group allocated at randomization. The stratification used for the randomization of clinics (TB caseload and type of facility) will be taken into account in the analysis.

##### Patient level

All patients recruited to the study will be used in the analysis of the primary and secondary outcomes. Patients will be analyzed as a member of the clinic in which he/she was recruited.

#### Analysis approach

The primary outcome will be measured at three time points: baseline, three and at six months. If a patient drops out, is not present on the day of the interview or refuses to answer questions the primary outcome at the end point of the trial will be missing. Therefore, except for the baseline measurement, no post-randomization information will be available for these participants. The extent of the missing component was estimated to be 10% at six months. The single follow-up measurement and the extent of the expected dropout has to be considered for the statistical method that can be used to provide an unbiased estimate of the intervention effect under the principle of intention to treat. The method that can be used to take account of the stratified cluster trial design, the repeated binary nature of the primary and secondary outcome (Risky drinking, TB treatment adherence, TB treatment outcome) and the missing data at follow-up is a weighted generalized estimation equations (WGEE) approach [35]. The method utilizes inverse probability weighting to correct for the bias associated with missing data that is not missing completely at random (MCAR) and participants with complete data are weighted with the dropout probability of participants with the same characteristics at baseline. To determine the weights a logistic regression model will be constructed for the dropout indicator utilizing measurements on the primary outcome (at baseline) and other variables taken at baseline or post-randomization. For comparison and checking an unweighted analysis will also be done.

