### Design

In order to assess the effectiveness of the Screening and Brief Interventions (SBI) among participants newly diagnosed with TB and found to be misusing alcohol, a cluster randomized controlled trial design will be implemented. All new TB patients will be screened using the Alcohol Use Disorder Identification Test (AUDIT). TB patients who meet the cut-off for misusing alcohol both in the intervention and control arms will be reassessed after baseline assessment at time 2 (3 months following intervention) and time 3 (6 months following intervention). The intervention will comprise the following: personalized feedback on AUDIT results, a health education leaflet, simple advice and brief counselling about reducing excessive drinking, during one -20 minute- session. The trial will incorporate cluster randomization of primary health care facilities to avoid the risk of contamination.

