###### Follow-up

The same measures as detailed above will be administered (at follow-up) to the intervention and control groups of patients at 3 months and again at 6 months after the baseline measures are obtained.

Broadly speaking then, the primary outcome measure of the study is: (1) change in the mean score on the AUDIT in the last 3 months and mean number of heavy drinking days in the last month of the study period compared with baseline, as measured by the AUDIT.

The secondary outcome measures of the study are: (1) anti-tuberculolisis treatment adherence and (2) successful TB response, classified by WHO as cured or treatment completed (versus treatment failure, defaulted, died or transferred out to another health facility [34].

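### The missing-data method rests on a single follow-up and no post-randomisation data for dropouts, but the AUDIT is taken at both 3 and 6 months, so 3-month outcomes risk going unused

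*Protocol article*

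**What the plan says.** The schedule is consistent wherever the protocol article describes it. Under Design, patients in both arms "will be reassessed after baseline assessment at time 2 (3 months following intervention) and time 3 (6 months following intervention". Under Follow-up, the baseline battery, which includes the AUDIT, is given again "to the intervention and control groups of patients at 3 months and again at 6 months after the baseline measures are obtained". The Analysis approach section opens the same way: "The primary outcome will be measured at three time points: baseline, three and at six months". The Procedure section adds a re-contact rule: "Even if a contact was not successful at 3 months, further attempts will be made at 6 months".

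The Analysis approach section then departs from this. It says that dropout, absence or refusal leaves the end-point outcome missing, and concludes that "except for the baseline measurement, no post-randomization information will be available for these participants". It continues: "The single follow-up measurement and the extent of the expected dropout has to be considered for the statistical method".

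On that footing it chooses weighted generalised estimating equations (GEE). Patients whose data are complete are weighted according to the dropout probability of patients with the same baseline characteristics. The weights come from one logistic model for a dropout indicator. In that model the primary outcome is named at baseline only, while other variables may be taken at baseline or after randomisation. An unweighted analysis is planned for comparison.

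**The concern.** The conclusion about dropouts does not follow from the design. A missing 6-month outcome does not mean that nothing was observed after randomisation, because the same instrument was due at 3 months. The two sentences are not incidental: they are the reason given for the method, so an analysis written from them would inherit the mistake.

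Two things are at stake. First, 3-month outcomes of patients lost by 6 months could go unused although they were collected. Second, weighting removes bias from dropout only to the extent that the weight model contains what drives dropout. In an alcohol trial, drinking after randomisation is a plausible driver, and the 3-month AUDIT is the planned measure of it. The weight model as worded does not name it.

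**Working it through.** **Step 1. The protocol's own numbers.** From Sample size calculation: 2600 screened × 0.20 positive = 520 enrolled; 520 × (1 − 0.10) = 468 remaining. Both figures reproduce exactly. The number lost is 520 − 468 = 52.

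**Step 2. The premise against the possible attendance patterns.** With two follow-up visits there are four:

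| 3 months | 6 months | Post-randomisation outcome observed? | Does the premise describe this patient correctly? |
|---|---|---|---|
| seen | seen | both visits | not applicable, end point observed |
| seen | missed | 3 months | **no**, the premise says there is nothing |
| missed | seen | 6 months | not applicable, end point observed |
| missed | missed | none | yes |

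The premise is true only of the last row. The second row is the group it misdescribes. The third row is made possible by the re-contact rule. These patients have the end-point outcome, so the premise does not touch them, but they show that missingness need not be monotone and that one dropout indicator does not describe it.

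**Step 3. How many patients fall in the second row.** Let *s* be the share of the 52 who were seen at 3 months. The protocol does not give *s*, so the range is shown.

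- Number with a 3-month outcome but no 6-month outcome = 52 × *s*
- Number with at least one follow-up = 468 + 52 × *s*

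| *s* (assumed) | 3-month outcome only | At least one follow-up |
|---|---|---|
| 0 | 0 | 468 |
| 0.5 | 26 | 494 |
| 1 | 52 | 520 |

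This takes the 10% as missing at six months, as the Analysis approach section does. Sample size calculation words it as loss before both follow-ups are completed. On that reading the 52 may include patients who missed only the 3-month visit, and the second row still cannot exceed 52.

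**Step 4. The weights.** Write R6 = 1 if the 6-month outcome is observed. As worded, the weight is built from P(R6 = 1 | baseline outcome, other variables). This corrects for dropout only if, given those variables, loss is unrelated to the 6-month outcome. If 3-month drinking predicts both loss and the 6-month outcome, and the other variables do not capture it, the condition fails. A model P(R6 = 1 | arm, baseline AUDIT, attendance at 3 months, 3-month AUDIT when observed) would remove that source of bias. The protocol contains nothing from which the size or direction of the bias could be calculated.

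**The case against.** The strongest reply is that the section contains enough to support a sound analysis. It refers to "the repeated binary nature of the primary and secondary outcome (Risky drinking, TB treatment adherence, TB treatment outcome", and a GEE for repeated outcomes can use each visit that was observed. It allows post-randomisation variables in the weight model. The Patient level section says "All patients recruited to the study will be used in the analysis of the primary and secondary outcomes". Finally, how visits enter the weights is detail that an article may leave to the full plan.

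The first three points stand as limits on the criticism. A reader might infer that observed outcomes will be discarded. No sentence orders that, and what counts as complete data is never defined as attendance at both visits. A reader might also infer that the 6-month outcomes of patients who missed only the 3-month visit are dropped. The text does not support this either: it defines missingness by the end-point outcome, which these patients have.

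The last point does not answer the criticism. The complaint is not that detail is absent but that the stated justification is wrong and conflicts with the same section's opening sentence. Allowing post-randomisation variables adds to the inconsistency, since the premise says that dropouts have no such information. The permission also covers only variables other than the primary outcome, which is named at baseline.

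**Conclusion.** The contradiction is real and should be corrected, because it sits in the reasoning for the primary analysis. The single follow-up and the absence of post-randomisation data are both incompatible with the two-visit schedule. Read literally, the method risks ignoring the 3-month outcomes of patients lost by 6 months and leaves 3-month drinking out of the weights.

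The group concerned is 0 to 52 of 520 patients, given the protocol's 10% loss and an unknown share seen at 3 months. The bias is conditional: it arises only if drinking after randomisation predicts loss, and its size is unknown.

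A loss of power should not be read into this. To compute one would need an AUDIT standard deviation, which the protocol does not give, and a rate of intermittent missingness, which it does not give either. Subtracting intermittent missers from 468 could also count them twice, because Sample size calculation can be read as already meaning patients who completed both visits.

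**What to change.** In the Analysis approach section:

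1. Delete the statement that patients missing the end point have only baseline information, and the reference to one follow-up measurement.
2. State that every observed 3- and 6-month outcome enters the repeated-measures weighted GEE, and identify the 6-month contrast between arms.
3. Replace the one dropout indicator with visit-specific observation weights. These should include arm, baseline AUDIT and, for the 6-month visit, the 3-month AUDIT when observed. Patients with only one follow-up then stay in, consistent with the Patient level section.
4. Keep the unweighted analysis for comparison.

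A linear mixed model on all observed scores is an option, not a required change; the weighted GEE can be kept. The cost is revised wording and modest programming. No new data are needed.

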#### Study hypotheses

• Individuals receiving the brief intervention will experience a greater change in mean number of AUDIT (alcohol risk) scores and mean number of heavy drinking days, compared with the individuals receiving a health education leaflet only (control group)

• Alcohol consumption (use and misuse) will be associated with anti-tuberculosis medication adherence and TB treatment outcomes.

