##### Patients with active TB

New tuberculosis treatment patients (i.e. those patients who have been initiated or have been on anti-TB treatment for less than one month), males and females, 18 years and above who visit the primary health care facility and who score 8 or more for men and 7 or more for women on the AUDIT questionnaire after screening will be included in this study. Some researchers found that brief interventions are effective even among excessive drinkers [21-23]. Therefore patients scoring high on the AUDIT are included in the study.

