#### Reporting

Estimated treatment effects (odds ratio and incidence rate ratio) will be reported with 95% confidence intervals.

Descriptive statistics will be calculated for baseline and follow-up. No significance tests will be performed at baseline.

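### The primary analysis is planned for binary risky drinking with ratio effect measures, but the trial is hypothesised and powered on mean AUDIT score, so the stated 80% power does not apply to it

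*Protocol article*

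**What the plan says.** The protocol article describes its primary outcome in several ways.

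- **Study hypotheses:** the intervention arm will show a "greater change in mean number of AUDIT (alcohol risk) scores and mean number of heavy drinking days".
- **Screening:** the primary measure is change in drinks per week, estimated from the first two AUDIT items.
- **Follow-up (under Outcome Measures):** the primary outcome is change in mean AUDIT score and in mean number of heavy drinking days.
- **Sample size calculation:** the starting mean is 12, and "it is assumed that the intervention will reduce the current AUDIT score by 12% to 10.6". The 452 patients are to give 80% power at the 5% level, "taking account of the design effect of 2 to account for intraclass correlations".
- **Analysis approach:** a weighted GEE is chosen partly because of "the repeated binary nature of the primary and secondary outcome (Risky drinking, TB treatment adherence, TB treatment outcome". The dropout model is built "utilizing measurements on the primary outcome (at baseline) and other variables taken at baseline or post-randomization".
- **Reporting:** "Estimated treatment effects (odds ratio and incidence rate ratio) will be reported with 95% confidence intervals".

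Entry is restricted to patients "who score 8 or more for men and 7 or more for women on the AUDIT questionnaire after screening will be included", and the Procedure section calls exactly these patients risky drinkers. That section also treats the screening AUDIT as the baseline assessment.

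**The concern.** The quantity that is hypothesised and powered is a difference in means, but the analysis and reporting sections plan no mean difference. A binary outcome with an odds ratio is a different estimand, and the article gives no expected proportion of risky drinkers at follow-up from which its power could be found. Dichotomising a score usually loses information, so the trial could be much weaker than stated for the test it plans to run. With three candidate primary scales in the text (mean score, drinks per week, binary status), the choice could also be made after the data are seen.

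The second issue is the baseline. If risky drinking means the AUDIT entry cut-off, every participant has the outcome at baseline in both arms. The baseline value of that outcome is then a constant. It cannot predict dropout, and it has no place as a response row in a repeated logistic model.

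**Working it through.** **Inputs from the article:** control mean 12; intervention mean 10.6 (difference 1.4; an exact 12% is 1.44); N = 452; design effect 2; 80% power; 5% level; 21 v 21 clinics; entry cut-off 8 for men and 7 for women.

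**Assumptions, because the article is silent:** a two-sided test; risky drinking means at or above the entry cut-off; the same design effect for the binary outcome; an SD back-solved from N.

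**1. The plan's own figure.** Effective n per arm = 452 / 2 arms / 2 (design effect) = 113. From n = 2(1.96 + 0.8416)² SD² / d²:

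- d = 1.4 gives SD = 1.4 × √(113/2) / 2.8016 = 3.76
- d = 1.44 gives SD = 3.86

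Forwards, SD 3.75 and d = 1.4 give 15.70 × 14.06 / 1.96 = 112.6, rounded up to 113 per arm, and 113 × 2 × 2 = 452. So 452 is consistent with an SD of about 3.8, but this is an inference and not a check against a stated value.

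**2. Power of the binary comparison, normal scores, controls at 12.** Worked case, cut-off 8, SD 3.76:

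- Control: z = (8 − 12)/3.76 = −1.06, so 85.7% are at or above the cut-off.
- Intervention: z = (8 − 10.6)/3.76 = −0.69, so 75.6%.
- Two-proportion test with pooled null variance, 113 per arm: (0.101 × √113 − 1.96 × 0.559) / 0.554 ≈ −0.04, so power is 48%.

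| Cut-off | d = 1.4, SD 3.76: proportions | Power | d = 1.44, SD 3.86: proportions | Power |
|---|---|---|---|---|
| 7 | 90.8% v 83.1% | 41% | 90.2% v 82.2% | 42% |
| 7.5 | 88.5% v 79.5% | 45% | 87.8% v 78.6% | 46% |
| 8 | 85.7% v 75.6% | 48% | 85.0% v 74.6% | 49% |

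With the 468 patients expected to complete follow-up (117 effective per arm), power is about 42-50%. Reaching 80% on this binary outcome under these assumptions would take about 940 to 1,190 patients.

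**3. Sensitivity.** Same back-solved SDs, 113 effective per arm, cut-offs 7 to 8:

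| Shape | Control mean 12 | Control mean 10 |
|---|---|---|
| Normal | 41-49% | 55-59% |
| Gamma | 60-69% | 72-75% |
| Lognormal | 67-77% | 79-84% |

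Normal scores with a control mean of 8 give about 60%. If the true SD were 5 or 6 (d = 1.4, controls at 12, normal), the comparison of means would itself have only 56% or 42% power, and the binary comparison about 31-34% or 24-26%.

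**4. Baseline.** Entry needs AUDIT at or above the cut-off, and the screening AUDIT is the baseline AUDIT. Under the assumed definition, the proportion of risky drinkers at baseline is 100% in both arms. A constant has no association with dropout, and the log-odds of a proportion of 1 is not finite.

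**The case against.** A reader might infer from the normal case that power simply falls from 80% to 40-50%. The article does not support that as a fact: it gives no SD, distribution or follow-up proportions. Scores cut off below at 7 or 8, with a mean of 12 on a 0-40 scale, suggest right skew, and controls often improve after screening. With both, the loss can be small or absent. This objection stands, and the size must be given as a range.

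A reader might also infer that the constant baseline breaks the treatment estimate. It need not. Analysis approach says the outcome is measured at baseline but does not say that baseline is a response row. If it were, only the baseline log-odds would be lost. In a simulated 42-clinic binary GEE with an independence working correlation, a common baseline and every baseline value positive, the intercept ran to 28.6. The treatment log odds ratio was −0.638 (SE 0.192), identical to the fit using follow-up only.

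Two further inferences go too far. The article does not exclude baseline AUDIT score: it is collected, and the dropout model allows other baseline variables. Nor is the incidence rate ratio clearly without use, since it may be meant for heavy drinking days. However, Reporting ties it to no outcome, and the AUDIT records frequency as a rated item and not as a count.

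Finally, Analysis approach does not define risky drinking. Equating it with the entry cut-off rests on the label in Procedure, though the article offers no other definition. The mismatch between a powered mean and a planned binary analysis does not depend on that reading.

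**Conclusion.** The plan is wrong as written. Its hypothesis, primary outcome under Follow-up and sample size concern mean AUDIT score, while its analysis and reporting sections provide a binary outcome and ratio measures. The powered quantity would not be estimated, and the 80% does not carry over to the planned test. This follows from the text alone.

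The size of the power loss is conditional. It is about 41-49% power with a back-solved SD near 3.8, normal scores, controls at 12 and the 7/8 cut-off, and about 40% to just over 80% across skewed shapes and lower control means. If risky drinking means the entry cut-off, its baseline value is uninformative for the dropout weights. That weakens the weighting as described but does not by itself bias the treatment effect.

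**What to change.** Reconcile Study hypotheses, Screening, Follow-up, Sample size calculation, Analysis approach and Reporting to one primary outcome and time point. The natural choice is the one the trial is powered on, AUDIT total score at 6 months, with drinks per week and heavy drinking days placed explicitly as secondary.

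- Analyse it with an identity-link weighted GEE or a linear mixed model clustered on clinic, with arm, baseline AUDIT score and randomisation strata as covariates. Report the adjusted mean difference with a 95% confidence interval.
- Define risky drinking, keep it as a secondary binary outcome, and model it at follow-up only.
- Name the continuous baseline AUDIT score as a predictor in the dropout model.
- Tie the incidence rate ratio to a named count outcome, such as heavy drinking days, or remove it.
- State the SD behind the 452.

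The cost is wording only. The AUDIT is already collected at baseline, 3 months and 6 months. If the sponsor does want the binary outcome as primary, the sample size must be redone with stated follow-up proportions.
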